## Abstract

**Introduction:**

Drug development for neurodegenerative diseases such as Friedreich’s ataxia (FRDA) is limited by a lack of validated, sensitive biomarkers of pharmacodynamic response in affected tissue and disease progression. Studies employing neuroimaging measures to track FRDA have thus far been limited by their small sample sizes and limited follow up. TRACK-FA, a longitudinal, multi-site, and multi-modal neuroimaging natural history study, aims to address these shortcomings by enabling better understanding of underlying pathology and identifying sensitive, clinical trial ready, neuroimaging biomarkers for FRDA.

**Methods:**

200 individuals with FRDA and 104 control participants will be recruited across seven international study sites. Inclusion criteria for participants with genetically confirmed FRDA involves, age of disease onset ≤ 25 years, Friedreich’s Ataxia Rating Scale (FARS) functional staging score of ≤ 5, and a total modified FARS (mFARS) score of ≤ 65 upon enrolment. The control cohort is matched to the FRDA cohort for age, sex, handedness, and years of education. Participants will be evaluated at three study visits over two years. Each visit comprises of a harmonized multimodal Magnetic Resonance Imaging (MRI) and Spectroscopy (MRS) scan of the brain and spinal cord; clinical, cognitive, mood and speech assessments and collection of a blood sample. Primary outcome measures, informed by previous neuroimaging studies, include measures of: spinal cord and brain morphometry, spinal cord and brain microstructure (measured using diffusion MRI), brain iron accumulation (using Quantitative Susceptibility Mapping) and spinal cord biochemistry (using MRS). Secondary and exploratory outcome measures include clinical, cognitive assessments and blood biomarkers.

**Discussion:**

Prioritising immediate areas of need, TRACK-FA aims to deliver a set of sensitive, clinical trial-ready neuroimaging biomarkers to accelerate drug discovery efforts and better understand disease trajectory. Once validated, these potential pharmacodynamic biomarkers can be used to measure the efficacy of new therapeutics in forestalling disease progression.

**Clinical trial registration:**

ClinicalTrails.gov Identifier: NCT04349514.

## Introduction

Friedreich’s ataxia (FRDA) is the most common inherited ataxia, with an estimated incidence in of 1 in 29,000 and a carrier frequency of 1 in 85 individuals of Caucasian background [1, 2]. Neurological features include progressive gait and limb ataxia, absent lower limb reflexes, extensor plantar responses, dysarthria and loss of position and vibration sense [3]. Non-neurological features include cardiomyopathy, visual and hearing impairments, diabetes mellitus, glucose intolerance and skeletal deformities [4]. Onset of FRDA occurs, on average, at 10–15 years, but may be delayed to the middle or later years of life.

The genetic cause of FRDA is mutation of the *FXN* gene, primarily in the form of homozygous GAA trinucleotide repeat expansions [5, 6]. The age of disease onset and associated severity of some symptoms is inversely correlated with the size of the GAA expansion on the smaller of the *FXN* alleles (GAA1) [7]. This genetic mutation results in reduced expression of frataxin, an essential protein in the Iron-Sulfur (FE-S) cluster complex, which disrupts iron homeostasis [8, 9]. Frataxin is highly expressed in the dorsal root ganglia (DRG), the spinal cord, cerebellar dentate nuclei, cerebral cortex, pancreas, heart, liver and skeletal muscle [5], reflecting the tissues most impacted in FRDA.

The neuropathology underlying FRDA is multifaceted and complex. Hypoplasia of large and small neurons of the DRG, as well as effects on the peripheral nerves and spinal cord are observed and suggests neurodevelopmental origin [10, 11]. Over time, atrophy of the dentate nucleus becomes apparent, significantly contributing to the neurological phenotype [10, 12, 13]. Abnormalities in cerebral structures [14–16], functions [17–20] and both intra-cerebral and cerebello-cerebral connectivity [17, 21–25] have also been reported in individuals with FRDA.

Currently, there are no approved disease-modifying treatments for FRDA. Trials to investigate new drugs typically employ broad measures of clinical and functional progression, which require large sample sizes and long observational periods to detect therapeutic efficacy [26–29]. Useful biomarkers that can more rapidly and sensitively identify tissue-specific effects, thus improving clinical trial efficiency, are therefore urgently required to enable early decision making and to support potential regulatory considerations.

There have been significant efforts over the last few years to build neuroimaging studies in FRDA, in order to track the trajectory of disease progression at the brain and spinal cord levels. This is evidenced in longitudinal studies such as IMAGE-FRDA [30, 31], which has provided crucial information on volumetric and microstructural changes in the cerebellar peduncles and brainstem [19, 20, 24]. Another longitudinal study provided information on volumetric, microstructural, and neurochemical changes in the spinal cord [32]. The ENIGMA-Ataxia project [33], a large cross sectional multi-site retrospective study, further helped identify regions altered in the brain at different stages of the disease. Collaborative work such as the European Friedreich’s Ataxia Consortium for Translational studies (EFACTS) [26–28], and the Friedreich’s Ataxia Clinical Outcome Measures (FACOMS) [34, 35] helped evaluate longitudinal changes in clinical assessment tools and develop assays to measure blood frataxin. Finally, the Human Connectome Project [36], and the standardised spinal cord imaging protocol (Montreal Protocol) [37] spearheaded the development of new, more efficient and standardised MRI protocols and analysis procedures.

This culmination of information and techniques from a range of existing studies has highlighted that neuroimaging measures of the brain and spinal cord are promising biomarkers of pharmacodynamic response to potential interventions within target tissues, and for tracking disease progression in FRDA [38]. Previous single site studies have shown associations between clinical severity and imaging measures such as the cross-sectional area of the cervical spinal cord [39], volume and iron content of the dentate nucleus [13, 40], microstructural integrity of the brainstem white matter [15, 24]. Furthermore, longitudinal measurements have shown that spinal cord morphometry (cross-sectional area), spinal cord fractional anisotropy, and spinal cord spectroscopy (ratio tNAA/mIns) are sensitive to disease progression in an early-stage cohort [32]. Importantly, longitudinal analysis has shown that particular neuroimaging measures may be more sensitive to FRDA progression at different stages of disease [13]. For example, the rate of change in iron concentration in the dentate nucleus accelerates with disease progression, whilst the rate of atrophy in this region is at its highest early in the disease course, plateauing over time [13]. Others have shown that clinical severity, genotype, age, and age at symptom onset influence the underlying neuropathology [15, 16, 24, 41]. Understanding the relationship between these parameters will therefore be crucial to establishing which neuroimaging biomarkers are most sensitive to disease progression, whether a biomarker is able to detect early onset of disease related symptoms and which biomarkers are most sensitive to potential treatments, within specific cohorts.

These previous studies have identified brain and spinal cord regions that may be compromised in FRDA, providing possible targets for interventional clinical trials, and biomarkers of disease progression. However, relatively small sample sizes, limited longitudinal follow up, and differing methodology at individual clinical research centres have limited the ability to achieve the necessary statistical power to detect significant changes, and to perform targeted sub-group analyses to better understand the neuropathology within specific cohorts. Furthermore, expanded longitudinal investigations are essential to distinguish developmental from degenerative changes, to identify the measurements most sensitive to clinical changes at different points in the disease trajectory and to more accurately relate imaging alterations with particular aspects of the complex clinical syndrome.

Disease trajectory mapping can also determine temporal changes that occur in FRDA and specific targets for future gene and cell therapy [42, 43], complementing the current gene therapy approaches treating cardiac complications in FRDA [43–45]. Furthermore, imaging biomarkers can be used as targets for potential therapeutics, such as those that augment mitochondrial function (Idebenone) [46, 47], or those that aim to increase frataxin levels (Erythropoietin) [48, 49], aiding in the evaluation of their efficacy, pharmacokinetic and pharmacodynamic properties [50].

In building on from this body of work, and understanding previous limitations, we conceived TRACK-FA: a longitudinal, multi-site and multi-modal neuroimaging natural history study designed to refine and validate potential neuroimaging biomarkers of FRDA progression. TRACK-FA will combine multiple imaging modalities–structural MRI, diffusion MRI, quantitative susceptibility mapping (QSM), and magnetic resonance spectroscopy (MRS)–to obtain complementary structural, microstructural and biochemical information on the brain and spinal cord in FRDA compared to control cohorts over 24 months. This combination of modalities will provide a more detailed picture of the underlying neuropathology in FRDA. Furthermore, its multi-site nature will facilitate the sample sizes needed to perform statistically powerful subgroup analysis.

TRACK-FA brings together global expertise in FRDA across academic, industry and advocacy groups to undertake the world-first prospective multi-site natural history study specifically to assess neurobiological changes underlying FRDA. TRACK-FA is scientifically governed by the TRACK-FA Neuroimaging Consortium and aims to accelerate the discovery of sensitive neuroimaging biomarkers of disease severity and progression to improve clinical trial efficiency.

## Methods and analysis

### Study aims

TRACK-FA aims to assess the potential value of imaging biomarkers and provide a scientific basis for instituting them in clinical trials for FRDA.

### Objectives

**Objective 1:** To determine the longitudinal sensitivity of a range of candidate neuroimaging biomarkers in the brain and spinal cord and identify the biomarker(s) most sensitive to change over time in individuals with FRDA compared to control participants.

**Objective 2:** To determine differences in candidate neuroimaging biomarkers and their time of change between children and adults with FRDA, and matched controls.

**Objective 3:** To determine change over time in clinical severity, cognitive function, mood, speech, and fluid markers such as blood Neurofilament Light Chain (NFL) and frataxin in individuals with FRDA compared to controls.

**Objective 4:** To determine the relationship between imaging biomarkers and clinical, cognitive, mood, speech and blood markers of disease severity, including age of onset, GAA repeat size, disease symptoms and duration, disease severity, frataxin levels and NFL in individuals with FRDA.

### Ethics statement

This study will be conducted in accordance with the Declaration of Helsinki (revised in 2013 by Fortaleza) and Ethical Guidelines for Medical Research Involving Human Subjects (partially revised on February 28, 2017).

This study has obtained approval from the institutional review boards (IRBs) at each of the study sites. The reference numbers for each study site are provided below.

Monash Health Human Research Ethics Committee (HREC): RES-20-0000-139A

Children’s Hospital of Philadelphia: IRB 20–017611

University of Minnesota: IRB STUDY00009047

University of Florida: IRB202000399

RWTH Aachen University: EK195/20

University of Campinas (CAAE NO): 83241318.3.1001.5404

McGill University (under review)

Potential participants will be provided with information about the study via an IRB-approved letter and information sheet. Research personnel will explain all study procedures to potential participants. Participants will be enrolled into the study upon obtaining written informed consent and meeting the inclusion and exclusion criteria (see below). Opt-in and opt-out systems are in place for all participants. All participant data will be de-identified upon enrolment into the study using a unique participant identifier. Each site will be required to ensure that participants are consented in such a way that allows the sharing of de-identified data (as outlined below).

### Data sharing

It is recognised that this project will generate data that are of interest to the FRDA academic and bio-pharmaceutical/drug development community. All de-identified data will be made available to consortium members after being generated, and then later to additional third parties at the completion of the study upon request, with approval from the TRACK-FA Steering Committee. All parties will have full access to the de-identified raw data throughout the study and interim reporting and final reports will be provided throughout the study in accordance with the milestones and deliverables.

All academic partners will provide access to their data to the TRACK-FA Neuroimaging Consortium members and the study funders, as well as the right to create derivative works of the research data. Up to date information regarding data sharing is available at the TRACK-FA website: Track-FA Study (monash.edu)

### Study design

The TRACK-FA study will involve the participation of children and adults with genetically confirmed FRDA and control participants. Participants will be allocated to one of four groups based on their age: ≥ 18 years, 11–17 years, 8–10 years, and 5–7 years. Control participants will be matched at the cohort level to the FRDA participants for age, sex, handedness, and years of education. A recruitment ratio of 1:1 (FRDA: control) will be used for those aged 5–10 years and a 2:1 ratio (FRDA: control) will be used for participants ≥ 11 years of age.

We aim to recruit a total of 200 individuals with FRDA and 104 control participants across seven testing sites. This number was informed by a power analysis (see below) and necessitated a multi-site collaborative network to achieve this goal. All participants will then be assessed at three visits [Visit 1 (V1), Visit 2 (V2), Visit 3 (V3)] with identical assessments; each visit will take place approximately 12 months apart and no more than two months before or after the 12-month interval.

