**Fig 1 pone.0269649.g001:**
[figure not shown]
Summary of TRACK-FA study procedures according to participant age. The testing schedule varies according to age. All participants will also undergo a speech assessment, whilst all FRDA participants will undergo additional clinical testing.

*Collection of medical and demographic information*. Medical history specific to FRDA will be taken in the enrolment session for all participants with FRDA. The following information will be collected: the length of *FXN* GAA repeat expansions on the smaller (GAA1) and larger (GAA2) allele, the type of mutation detected, age of symptom onset including first symptom, disease duration, presence of diabetes and medical information pertaining to nervous system disorders (apart from FRDA), heart conditions, vision impairments, skeletal abnormalities (scoliosis and foot deformities), hearing conditions, bowel and bladder conditions, presence of inflammatory diseases, details on concurrent trial participation and COVID-19 status.

The following information will be collected for all participants: height and weight (used to calculate body mass index (BMI), and medications (prescription/non-prescription).

*MRI scanning to assess primary outcomes*. All participants will undergo brain and (cervical) spinal cord imaging procedures lying supine in a three tesla (3T) MRI scanner (Siemens Skyra, Siemens Prisma or Philips Ingenia). Significant effort has been made to ensure harmonisation of MR protocols across all the sites with vigorous testing of the imaging sequences prior to the commencement of the study. The inclusion of QSM, diffusion MRI and MRS in the procedure allows for the quantification of iron accumulation, microstructural and neurochemical profile of areas pertinent to disease pathology [39], potentially providing further insights into neuronal damage and gliosis associated with the neurodegenerative nature of this disease [32].

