Depending on age, one of two MRI protocols will be used: the first protocol, approximately 90 minutes long, will be used in all participants aged >10 years. The second, approximately 30 minutes long and designed to be less taxing for younger children, will be used in the 5–10 years age group. The young child protocol only includes anatomical scans (brain and spinal cord), but no diffusion MRI, brain QSM, or spinal cord MRS. Brain T1, T2 and diffusion acquisitions are based on those used in the Human Connectome Project [36]. Brain QSM acquisition was optimised to provide excellent image quality and contrast with 0.9 isotropic resolution. The spinal cord T2, diffusion and MEDIC acquisitions are based on a recently published spinal cord protocol [37]. The spinal cord MRS is based on a semi-LASER sequence developed at the University of Minnesota [54], with addition of metabolic cycling. The specific MR sequences, acquisition time, and key parameters for each sequence are outlined below in Table 3. These sequences will be used to acquire the outcome measures provided in Table 4.

**Table 3 pone.0269649.t003:** TRACK-FA protocol used to obtain cervical spinal cord and brain MRI data.

Data	Sequence	Resolution	Main parameters	Acq. time
Spine T2	3D SPACE	0.8 mm iso	TE 120 ms, TR 1500ms, iPAT 3	4’02”
Spine MRS battery (includes power calibration and shimming)	semiLASER (CMRR)	8 x 6 x 33 mm	TE 30 ms, TR 2500 ms, NA 160	8’10””
Spine diffusion	2D SE-EPI with ZOOMit	0.9 x 0.9 x 5mm	TE 61 ms (Skyra 92ms), TR 620 ms (Skyra 680 ms), 5 concatenations, 30 dirs, b = 800, 5 b0 On Skyra, NT = 2 for diffusion weighted volumes (b = 800)	4‘(AP) + 1’ (PA) (b0 only) (with pulse trigger) On Skyra these times are nearly doubled)
Spine MEDIC	2D multi-echo	0.5 x 0.5 x 5mm	TE 14 ms, TR 600 ms, NA 2, 3 echoes, iPAT 2	4’45”
Brain T1	3D MPRAGE	0.8 mm iso	TE 2.2ms, TR 2400 ms, TI 1000 ms, iPAT 2	6’38”
Brain T2	3D SPACE	0.8 mm iso	TE 563ms, TR 3200 ms, iPAT 2	5’57”
Brain diffusion	Multiband EPI (CMRR)	1.5 mm iso (Skyra 1.7 mm iso)	TE 89ms (Skyra 102 ms), TR 3230 ms (Skyra 3366 ms), MB 4, 197 dirs, 2 shells, b = 1500/3000, 6 b0	5’37” (AP) + 5’37” (PA)
				Skyra 5’52” (AP) + 5’52” (PA)
Brain QSM	3D GRE	0.9 mm iso	TE1/TE2/TE3/TE4 = 3.7/9.7/15.8/21.9 ms, TR 27ms, iPAT 2	7’22”

* For participants 10 years old and younger, only anatomical data (highlighted in grey) are collected.

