### Status and timeline of the study

TRACK-FA participant recruitment will occur throughout the period of January 2021 to October 2022. As of September 2021, total of a total of 27 individuals with FRDA consisting of 21 adult participants with FRDA, five older paediatric participants with FRDA and 1 younger paediatric participant with FRDA, have been tested. A total of 11 control participants have been tested.

The target recruitment statistics for the 18-month period will include a total of 200 participants with FRDA, including 110 adult participants with FRDA, 82 participants with FRDA of age 11–17 and eight total participants of age 5–10 (Fig 2).

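### The two recruitment ratios give controls nearly twice the share of 5–10-year-olds (7.7% against 4.0%), and the pooled comparisons of change do not name age group

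*Protocol article*

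**What the plan says.** The Study design section of the protocol article states the matching rule: "Control participants will be matched at the cohort level to the FRDA participants for age, sex, handedness, and years of education". The same paragraph sets two ratios. For the youngest, "A recruitment ratio of 1:1 (FRDA: control) will be used for those aged 5–10 years"; for everyone else, "a 2:1 ratio (FRDA: control) will be used for participants ≥ 11 years of age". The overall target is given next: "We aim to recruit a total of 200 individuals with FRDA and 104 control participants across seven testing sites".

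The section on status and timeline splits the 200 FRDA participants as "110 adult participants with FRDA, 82 participants with FRDA of age 11–17 and eight total participants of age 5–10".

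Two analyses compare change between the groups. The section on difference-in-difference analyses takes each person's 12-month change and compares the groups with a two-sample t-test or a Mann-Whitney test. The section on longitudinal changes fits a mixed model with a random slope per participant and tests a fixed effect for the FRDA–control difference in mean slope; it names no age term. By contrast, the adjusted baseline comparison does use demographic covariates, and the model that examines site differences at baseline includes age.

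Participants aged 10 or younger have anatomical scans only, and Table 4 stars the measures restricted to those over 10.

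**The concern.** A cohort-level age match and a ratio that changes with age cannot both hold for the pooled groups. If the youngest children are sampled at 1:1 and everyone else at 2:1, the control group must contain a larger share of young children than the FRDA group.

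This is harmless where the analysis is made within age group. It matters where the groups are pooled and the outcome is change over time, because children aged 5–10 may change at a different rate from adolescents and adults for reasons unrelated to FRDA. Part of the pooled FRDA–control difference in change would then reflect age mix. Objective 1 rests on that contrast.

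**Working it through.** **Inputs (protocol article).** FRDA targets of 110 adults, 82 aged 11–17 and 8 aged 5–10 (status and timeline). Ratios of 1:1 at ages 5–10 and 2:1 from age 11, with 104 controls in all (Study design). Measures by age restriction (Table 4).

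**1. Reproduce the stated number of controls.** 110/2 + 82/2 + 8/1 = 55 + 41 + 8 = 104. This agrees with the article, so the ratios and targets are the ones the plan used.

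**2. Age mix of each group.**

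| Age group | FRDA (n = 200) | Controls (n = 104) |
|---|---|---|
| 18 and over | 110 (55.0%) | 55 (52.9%) |
| 11–17 | 82 (41.0%) | 41 (39.4%) |
| 5–10 | 8 (4.0%) | 8 (7.7%) |

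The gap in the share aged 5–10 is 8/104 − 8/200 = 0.0769 − 0.0400 = 0.0369. Above age 10 the mix is the same in both groups: 110:82 in FRDA and 55:41 in controls, with totals of 192:96, exactly 2:1. The youngest stratum is therefore the only source of age-group imbalance by design.

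**3. Which measures are affected.** Table 4 lists 17 imaging measures. Six are taken at all ages: total brain, white matter, grey matter, cerebellar and superior cerebellar peduncle volumes, and cervical cord cross-sectional area. The other 11 (two from susceptibility mapping, four from brain diffusion, four from cord diffusion, one from spectroscopy) are restricted to participants over 10 and are balanced at 192:96.

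**4. Size of the bias.** Let D be the difference in mean change between ages 5–10 and the rest, in SD of change, taken as equal in both groups. Let δ be the true FRDA–control difference.

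- FRDA mean = rest + δ + 0.0400 × D
- Control mean = rest + 0.0769 × D
- Crude contrast = δ − 0.0369 × D

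The article gives no rate of change by age, so D is an assumption:

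| Assumed D (SD) | Size of bias (SD) | Relative to 0.3 |
|---|---|---|
| 0.25 | 0.009 | 3% |
| 0.5 | 0.018 | 6% |
| 1 | 0.037 | 12% |
| 2 | 0.074 | 25% |

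The last column uses the planning effect size of 0.3 as a rough yardstick only. The sample size section defines it for a change in each parameter, not for an FRDA–control contrast.

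**5. Check on the cause.** A single 2:1 ratio would give 55 + 41 + 4 = 100 controls, with 4/100 = 4.0% aged 5–10, the same as in FRDA. The whole imbalance comes from four additional young controls.

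**The case against.** The 1:1 ratio in the smallest stratum is a sensible choice: it gives eight FRDA children and eight controls, where 2:1 would give eight and four. The article never says that the pooled groups will be analysed without regard to age for every purpose. Objective 2 compares children and adults with matched controls, and the baseline analysis is run across age groups. An article condenses the full plan, so silence on covariates in the slope model may mean only that they are listed elsewhere. The bias is also small unless young children change very differently from everyone else.

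Most of this stands. The ratio should stay, the size is modest, and the silence of the slope model is weak evidence by itself. The 12-month comparison does not rest on silence, however: the article names the test, and that test takes no covariates.

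Two stronger readings are tempting, and the documents support neither.

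- *Scanner imbalance and drift.* The matching list omits site, scans use a "three tesla (3T) MRI scanner (Siemens Skyra, Siemens Prisma or Philips Ingenia", and brain diffusion resolution is "1.5 mm iso (Skyra 1.7 mm iso". A reader might infer that the groups differ in scanner mix and that scanner drift biases the contrast. Recruitment across the seven sites is in Fig 2, which is not shown, so an imbalance cannot be asserted. A fixed additive acquisition difference cancels in within-person change if a participant stays on one scanner. The plan also harmonises protocols, processes each modality at one site, tests for site differences, adds a random site effect where they are found, and runs monthly phantom checks at every site. Any figure for imbalance or drift would be pure assumption.
- *Bias towards an FRDA deficit.* A reader might infer that growth makes the control slope more positive. The article gives no growth rate or direction for any of the six measures, and the sign may differ between them.

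**Conclusion.** The point holds as a minor inconsistency between design and analysis. On the plan's own targets, the pooled groups are not matched on age: 4.0% of FRDA participants and 7.7% of controls are aged 5–10. The stated 12-month test does not correct for this, and the slope model as described does not name a term that would.

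The consequence is confined to six of the 17 imaging measures. Its size is 0.009 to 0.074 SD for assumed gaps in change of 0.25 to 2 SD, with unknown direction. These figures assume that the recruitment targets are met, that dropout does not alter the age mix, and that the gap in change between young children and the rest is the same in both groups. The point does not threaten the study's conclusions, but it is easily removed, and the reason to remove it is structural: the sampling ratio differs by age group, so a pooled contrast should take age group into account.

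**What to change.** Keep the 1:1 ratio at ages 5–10, and state in the Study design section that the age match is meant within age group rather than for the pooled cohorts.

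In the slope model, include recruitment age group (5–10, 11–17, 18 and over) and its interaction with time as fixed terms. The interaction is the part that matters, because an age main effect alone shifts levels and leaves the slope contrast unadjusted. Ages 5–7 and 8–10 can be combined, since both are recruited at 1:1 and together hold only eight participants per group. For the 11 measures restricted to participants over 10, the youngest level simply drops out.

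For the 12-month comparison, replace the plain t-test with a linear model of change on group and age group, and the plain Mann-Whitney test with its stratified form (van Elteren).

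With three age groups the cost is four fixed-effect parameters in the slope model (two for age group, two for its interaction with time) and two in the 12-month model. No change to recruitment is needed.
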